## Methods and design

Purposive sampling will be used for this prospective mixed method study. Patients who have previously attended the outpatient physiotherapy department for the management of their orthopaedic, NMS and paediatric conditions prior to the national lockdown and those who had to have their appointments cancelled will be invited to participate. These patients will be selected as they are long-term patients requiring ongoing physiotherapy to prevent further disability but are not prioritised for face-to-face consultations because of the COVID-19 pandemic. Initially, a pilot study will be conducted to determine the sample size and rule out any errors in the methodology, and thereafter the study will be expanded.

A standard operating procedure (SOP) will be developed for arthroplasty (orthopaedic) and patients with chronic low back pain (NMS), cerebral palsy, developmental delay and acute orthopaedic conditions (paediatrics) with the purpose of providing an outline for therapists to deliver telerehabilitation services effectively and ethically. For each area, a database will be created containing videos and images of relevant interventions related to the specific condition being treated. Exercise prescription will commence from the patients’ current level of function and will be progressed as per the criteria described in the section’s guidelines of management of arthroplasty, chronic low back pain and paediatric patients. A section on general advice and health education will also be included.

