#### Outcome measures

The Hip Disability and Osteoarthritis Outcome Score Joint Replacement (HOOS JR), which is a self-reported questionnaire on performance pain and functional status, with good reliability and construct validity, will be used for patients with hip arthroplasty (Lyman et al. 2016). The Knee Injury and Osteoarthritis Outcome Score (KOOS JR) will be used for knee arthroplasty patients. The KOOS JR is a knee-specific outcome measure assessing pain, symptoms and function related to their knee and associated problems (Lyman et al. 2016). The KOOS has been validated in multiple populations, activity levels and ages. Divergent and convergent construct validities have been determined when comparing to the SF-36 a health survey. The HOOS JR and KOOS JR will be used as an objective outcome measure for participants with arthroplasty.

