### Statistical analysis

All identifiers will be removed. Descriptive statistics will be used to analyse the gathered data during the time of the study. Frequencies and percentages for categorical data and means and standard deviations or medians and percentiles for numerical data will be calculated. The data will be tabulated; trends will be presented in the form of graphs. A statistician assisted with the planning of data analysis. The statistical analysis for each objective will now be presented:

1.To determine the effects of telerehabilitation services for patients who have orthopaedics conditions (arthroplasty).

Categorical variables (symptoms, pain, function and daily living, function, sports and recreational activities, quality of life) will be summarised by using frequencies and percentages. Bivariate analysis between groups for total hip replacements and total knee replacements will be performed by using Chi squared test if 25% of the expected frequencies are above five or by using Fisher’s exact test if the assumption is not valid. Similarly, bivariate associations between gender, age and compliance with the outcomes (symptoms, pain, function and daily living, function, sports and recreational activities, quality of life) will be assessed by using Chi squared test or Fisher’s exact test:

2.To determine the effects of telerehabilitation services for patients who have NMS conditions (chronic low back pain).

Categorical variables (symptoms, pain, function and daily living, function, sports and recreational activities, quality of life) will be summarised by using frequencies and percentages. Whilst age is a continuous/numerical variable and the outcomes being categorical variables, with three groups, an analysis of variance (ANOVA) test is used if data are normally distributed or Kruskal Wallis test is used if they are not normally distributed:

3.To determine the effects of telerehabilitation services for patients who have paediatric conditions.

Categorical variables will be summarised by using frequencies and percentages:

4.To determine the patient or caregiver and physiotherapist experiences in the rollout of telerehabilitation services.

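### Arthroplasty outcomes are planned as categorical and tested only by chi-squared or Fisher's exact test, although the named outcome measures are scores; no test of the scores is planned

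*Protocol article*

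**What the plan says.** Under the arthroplasty heading, Outcome measures names two instruments. The hip instrument is introduced as "The Hip Disability and Osteoarthritis Outcome Score Joint Replacement (HOOS JR), which is a self-reported questionnaire on performance pain and functional status". For the knee, "The KOOS JR is a knee-specific outcome measure assessing pain, symptoms and function related to their knee and associated problems". Their role is then fixed: "The HOOS JR and KOOS JR will be used as an objective outcome measure for participants with arthroplasty".

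Statistical analysis opens with a general provision for numerical variables: "means and standard deviations or medians and percentiles for numerical data will be calculated". Item 1, on arthroplasty, says: "Categorical variables (symptoms, pain, function and daily living, function, sports and recreational activities, quality of life) will be summarised by using frequencies and percentages". It continues: "Bivariate analysis between groups for total hip replacements and total knee replacements will be performed by using Chi squared test", with Fisher's exact test as the fallback. The same pair of tests is used for "bivariate associations between gender, age and compliance with the outcomes (symptoms, pain, function and daily living, function, sports and recreational activities, quality of life".

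Item 2, on chronic low back pain, describes age as a numerical variable and compares it across three outcome groups by ANOVA or Kruskal-Wallis.

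No sample size is given. Methods and design says: "Initially, a pilot study will be conducted to determine the sample size and rule out any errors in the methodology".

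**The concern.** An instrument that yields a score is named as the outcome measure, but the analysis of that objective has no place for a score. If the listed outcomes are the HOOS JR and KOOS JR results, a chi-squared test can use them only after they have been cut into bands. Patients just either side of a cut then count as different, and patients far apart within one band count as the same. The comparisons by joint, gender, age and compliance lose power, and a percentage in a band says less than a mean or median score with its interval.

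Age raises the same problem independently. Item 1 has to band it to run the stated tests, while item 2 keeps it numerical. Nothing in the article explains the difference.

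**Working it through.** **Step 1: the passages side by side.** The arthroplasty section describes the two instruments as covering pain, symptoms and function. Item 1 lists symptoms, pain, two function entries, sports and recreation, and quality of life. The last two appear in neither instrument's description, and no sentence says which instrument supplies which variable. Three readings are possible:

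| What the listed outcomes are | Consequence of the stated tests |
|---|---|
| HOOS JR / KOOS JR scores in bands (the natural reading) | Information in the score is discarded |
| Ordered item responses, categorical as collected | Chi-squared ignores the order |
| Something other than these instruments | The named outcome measures have no planned test |

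None of the three leaves item 1 sound as written. The inconsistency over age holds under all of them, because item 2 shows a way to relate numerical age to a categorical outcome.

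**Step 2: what banding would cost.** The plan has no power figure to reproduce. Everything below is assumed: normal score, equal SDs, two equal groups of n, two-sided 5%, standardised difference d.

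*Score analysed directly.* Power = Φ(d√(n/2) − 1.96). With d = 0.5 and n = 63: 0.5 × √31.5 = 2.806; 2.806 − 1.960 = 0.846; Φ(0.846) = 80.1%.

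*Median split, chi-squared.* The proportions above the cut are 1 − Φ(0.25) = 0.401 and 1 − Φ(−0.25) = 0.599, a difference of 0.1974. SE under the null = √(2 × 0.5 × 0.5/63) = 0.0891. SE under the alternative = √(2 × 0.401 × 0.599/63) = 0.0873. Power = Φ[(0.1974 − 1.96 × 0.0891)/0.0873] = Φ(0.261) = 60.3%. Loss: 80.1 − 60.3 = 19.8 points.

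*k equal bands.* Noncentral chi-squared with k − 1 df and λ = n Σ[(a − p)²/p + (b − p)²/p], where a and b are the two groups' band probabilities and p is their mean.

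Results at d = 0.5 and 63 per group, against 80.1% on the score:

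| Categorisation | Power | Loss (points) |
|---|---|---|
| Median split, chi-squared | 60.3% | 19.8 |
| Median split, Fisher's exact (full enumeration) | 57.0% | 23.1 |
| Three equal bands | 58.8% | 21.3 |
| Four equal bands | 55.7% | 24.4 |
| Five equal bands | 52.5% | 27.6 |
| Split at 75th percentile | 52.8% | 27.3 |
| Split at 90th percentile | 35.9% | 44.2 |

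With power on the score kept at about 80%, the median split gives 60.7% at d = 0.3 (175 per group) and 59.9% at d = 0.8 (25 per group), so the 60% figure does not depend much on d.

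**Step 3: how the loss moves with group size** (d = 0.5, median split, chi-squared):

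| n per group | Score | Median split | Loss (points) |
|---|---|---|---|
| 10 | 20.0% | 13.6% | 6 |
| 20 | 35.2% | 23.4% | 12 |
| 30 | 49.1% | 33.0% | 16 |
| 50 | 70.5% | 50.6% | 20 |
| 100 | 94.2% | 80.2% | 14 |
| 200 | 99.9% | 97.9% | 2 |

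At d = 0.5 the loss therefore runs from about 2 to about 44 points. The most extreme case at d = 0.8 (33 per group, 90th-percentile split) goes a little further: 90.1 − 43.4 = 46.7 points. Few patients fall in the upper band there, so the approximation is rough. Power was lower after categorising in every scenario.

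**The case against.** The strongest reply is that a reader might infer a loss of about 20 points as a property of this plan, and the article does not support that. It states no sample size, alpha, effect, number of categories or cut-point, and leaves the sample size to a pilot. Twenty points belongs to a median split or three bands with power on the score near 80%. At d = 0.5, small groups lose fewer points and very large groups almost none. This stands, and the figure is used here only as an illustration.

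A reader might also infer that the article plans to cut the HOOS JR and KOOS JR into bands. It never says so. The listed variables could be item responses that are categorical as collected, and the banding calculation would then not apply. This also stands, but it does not rescue item 1: chi-squared would ignore the order of such responses, or the named instruments would have no test.

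Third, the absence of cut-points cannot be a finding. A condensed article may leave category definitions to the full protocol or analysis plan. Accepted. The point concerns what item 1 does state: the variable type, the summary and the tests.

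Fourth, the opening sentence on numerical data may still yield a mean or median score. That is possible, so it would be too strong to say that scores will be reported only as percentages. But that sentence is descriptive, is not tied to these instruments and supplies no test.

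Finally, this is a purposive-sample, mixed-method study with largely descriptive aims and no power target, so power is a limited yardstick. That tempers the seriousness. Item 1 nevertheless plans formal group comparisons, and an inefficient choice there gains nothing.

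**Conclusion.** The point holds in this form: the arthroplasty outcome measures are scores, item 1 treats the arthroplasty outcomes as categorical, it does not map its domains to the instruments, and it plans no test of the score. The differing treatment of age in items 1 and 2 is an inconsistency in its own right.

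The size cannot be fixed from the article. Under the assumptions above, and only if the scores are banded, 80% power falls to about 60% with a median split. At d = 0.5 the loss ranges from about 2 to 44 points, depending on group size and cut. The direction was the same in every scenario. This is worth correcting because it is nearly free. It is not a flaw that invalidates the study.

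**What to change.** Replace the categorical treatment in Statistical analysis, item 1, with wording such as:

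> HOOS JR (hip) and KOOS JR (knee) will be analysed as numerical scores within each instrument, summarised by mean and SD or median and quartiles with 95% CI. Associations with gender and compliance group will be tested by t-test or Wilcoxon rank-sum test (ANOVA or Kruskal-Wallis if there are more than two compliance groups), and with age as a numerical variable by Pearson or Spearman correlation. Hip and knee results will be shown side by side; scores from the two instruments will not be pooled or tested directly against each other.

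Keep chi-squared and Fisher's exact test for variables that are truly categorical. If any of the listed domains is retained, state which instrument supplies it.

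The cost is one paragraph of rewording, with no new data, patients or staff. Banded percentages can still be shown descriptively. The one real loss is that the formal hip-versus-knee test becomes a descriptive comparison for these scores, and the text should say so.

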### Objectives

The objectives of the study are as follows:

To determine the patient and/or caregiver and physiotherapist experiences in the rollout of telerehabilitation for selected outpatient groups.To determine the effects of telerehabilitation services for patients who have orthopaedic conditions (arthroplasty), NMS conditions (chronic low back pain) and paediatric conditions (cerebral palsy, developmental delay and orthopaedic conditions).

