Frequencies and proportions will be used to summarise categorical variables. The two samples proportions test will be used to compare if there are any differences between the Yes or No responses. Comparisons between proportions with categorical variables will be performed by using the Chi squared test with the condition that the assumption is met:

5.Qualitative information will be gathered from two sources. The therapist’s experiences will be collected as positive, negative, challenges and other, and if further subthemes emerge from those categories, it will be described verbatim. In the subjective framework of questions, patients are asked a directed open-ended question on their experience of the call and the telerehabilitation sessions. The responses will also be categorised into themes that emerge.

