Findings will be disseminated by means of publications in relevant accredited journals like the South African Health System Review to advise policymakers on the efficacy of such systems. It will be presented at various conferences and symposiums and, in addition, will be presented in several forums like Physiotherapy Forum, Rehabilitation Forum, CHBAH Research Day, Ekurhuleni Research Day and other symposiums to disseminate the information in the context it was studied on.

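### No primary outcome, time point or contrast is named for any clinical group, while about 21 to 30 bivariate tests without an exploratory label are fixed under the effects objectives

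*Protocol article*

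**What the plan says.** The second objective is "To determine the effects of telerehabilitation services for patients who have orthopaedic conditions (arthroplasty), NMS conditions (chronic low back pain) and paediatric conditions". No outcome, time point or comparison is singled out as deciding it.

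The earlier sections do name instruments. Arthroplasty patients complete the HOOS JR or the KOOS JR, according to the joint. The low back pain section makes the Keele STarT Back tool its outcome measure at every session. Appendix 4 sets a paediatric goal and reviews it at 3 months.

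The Statistical analysis section undertakes to give the analysis for each objective, but refers to none of these instruments.

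- **Item 1 (arthroplasty):** "Bivariate analysis between groups for total hip replacements and total knee replacements will be performed by using Chi squared test", or by Fisher's exact test. The same tests are planned for "bivariate associations between gender, age and compliance with the outcomes (symptoms, pain, function and daily living, function, sports and recreational activities, quality of life".
- **Item 2 (low back pain):** the same list of domains is summarised, and then "Whilst age is a continuous/numerical variable and the outcomes being categorical variables, with three groups, an analysis of variance (ANOVA) test is used", with Kruskal-Wallis as the alternative.
- **Item 3 (paediatrics):** frequencies and percentages only.
- **Item 4 (experience):** Yes and No responses are compared, and "Comparisons between proportions with categorical variables will be performed by using the Chi squared test with the condition that the assumption is met".

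No significance level is given and no test is called exploratory. The Discussion says findings will be published "to advise policymakers on the efficacy of such systems".

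**The concern.** A reader cannot tell which quantity answers the effects objective in any group. The domains in items 1 and 2 are not the instruments' scores. The protocol describes the KOOS JR as covering pain, symptoms and function, yet the list adds sport and quality of life. It then reuses the list for low back pain, where the named tool is a risk-screening score.

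If the plan is followed as written, the only inferential output under the arthroplasty and low back pain effects headings is a set of p-values for associations with joint, gender, age and compliance. With many such tests and no deciding outcome, whichever association crosses the threshold can become the headline result of an effects objective.

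**Working it through.** The document states no sample size, power, alpha or error rate, so there is no figure of its own to reproduce.

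**Step 1. Count the tests in items 1 and 2.**

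- The outcome list has six entries as punctuated, or five if function, sports and recreational activities form one domain.
- Arthroplasty has four contrasts (hip versus knee, gender, age, compliance): 4 × 5 = 20 or 4 × 6 = 24 tests.
- Low back pain has one age test if the three groups are the STarT Back risk categories, or 5 to 6 if age is tested against each listed domain.
- Lowest total: 20 + 1 = 21. Middle: 20 + 5 = 25. Highest: 24 + 6 = 30.

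**Step 2. Assumptions.** Two-sided 5% per test, every null true, and normally distributed test statistics.

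**Step 3. Independent tests.** Chance of at least one false positive = 1 − 0.95^m, for m tests.

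- m = 21: 1 − 0.95^21 = 65.9%
- m = 25: 1 − 0.95^25 = 72.3%
- m = 30: 1 − 0.95^30 = 78.5%

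The expected number of false positives is 21 × 0.05 = 1.05 to 30 × 0.05 = 1.5.

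**Step 4. Correlated outcomes.** Domains measured on the same patients are correlated. This was simulated (200,000 runs) with equal correlation between outcomes within each contrast and independence between contrasts.

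| Tests | Correlation 0.5 | Correlation 0.8 |
|---|---|---|
| 20 (arthroplasty, 4 blocks of 5) | 55.5% | 41.9% |
| 21 (add one independent age test) | 1 − 0.445 × 0.95 = 57.7% | 1 − 0.581 × 0.95 = 44.8% |
| 25 (5 blocks of 5) | 63.6% | 49.5% |
| 30 (5 blocks of 6) | 68.8% | 52.7% |

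**Step 5. Sensitivity to alpha, independent tests.**

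- At 0.01: 1 − 0.99^21 = 19.0% to 1 − 0.99^30 = 26.0%.
- At 0.10: 1 − 0.90^21 = 89.1% to 1 − 0.90^30 = 95.8%.

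**Step 6. What is left out.** Item 4 adds Yes/No comparisons: nine caregiver items in Appendix 5 have Yes/No answers, or eight without item 3, which asks what was difficult. It also adds chi-squared comparisons that cannot be counted. They are excluded because a Yes/No split away from one half is plausible on satisfaction items, so significance there need not be a false positive.

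**The case against.** **The study is largely descriptive.** Sampling is purposive, the analysis opens with descriptive statistics, effectiveness is to be explored, and the abstract's conclusion concerns feasibility. Formal multiplicity control is often not expected in such a study, and a correction method may sit in an analysis plan that is not shown. This stands as far as it goes, so the absence of a correction is not the point made here. Which outcome decides an objective is protocol content, however, and the section prescribes specific tests under effects headings without calling them exploratory.

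**Instruments are named.** Low back pain has one tool and each arthroplasty patient one joint-specific score. That is true, but no planned analysis uses either.

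**The probabilities are soft.** Alpha is assumed, and at 0.01 the figure falls to 19% to 26%. Fisher's exact test is conservative in small samples and would lower it further. If the four arthroplasty contrasts are themselves associated, it also falls: one common correlation of 0.5 across all 20 arthroplasty tests gives about 42%. These caveats stand.

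**Two stronger readings are tempting.** A reader might count at least 33 tests. That needs eight caregiver items added to 25, and it is not a minimum: with one age test in low back pain the same sum is 20 + 1 + 8 = 29. A reader might also infer that a chance positive would be an efficacy result. None of the counted tests is a before-after or controlled comparison, so the documents do not support that.

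**Conclusion.** The point holds in a limited form. No outcome, time point or contrast is designated as answering the effects objective in any group, and the planned tests are detached from the instruments collected.

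Items 1 and 2 fix 21 to 30 tests. At an assumed 5% each and with all nulls true, the chance of at least one false positive is about 66% to 79% under independence, 58% to 69% at a within-contrast correlation of 0.5, and 45% to 53% at 0.8. A chance positive is therefore more likely than not over much of this range, but not at high correlation or a stricter alpha. It would be a spurious subgroup association. The remaining risk is misreading, because it would be reported under an effects heading in a study meant to advise on efficacy.

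**What to change.** In the Statistical analysis section:

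- Name one primary outcome per clinical group from data already collected. Examples are the HOOS JR or KOOS JR total score for arthroplasty, the STarT Back total score for low back pain, and goal attainment at 3 months for paediatrics.
- State the summary that answers the objective: change from the first session to a defined assessment, or the proportion attaining the goal, with a 95% confidence interval. A primary label alone would not suffice, since no change analysis is planned at present.
- Let the sponsor choose an assessment point that fits the variable visit intervals and goal-based discharge. For low back pain, note that the STarT Back score also governs discharge and routing to face-to-face care. A score taken at discharge under the stated criterion would be below three by construction.
- Label all hip/knee, gender, age, compliance and item-level experience tests exploratory, report them as estimates with 95% confidence intervals, and draw no effect or efficacy conclusion from their p-values.

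The cost is wording, plus a decision on the assessment point; no new patients or instruments are needed. The downside is that an isolated significant subgroup or domain result can no longer be presented as a finding.

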### Specific procedure for each of the conditions follows orthopaedic physiotherapy (arthroplasty)

#### Procedures

A database of exercises will be created with different categories and levels of exercises that include range of motion, strength and balance and are subdivided into easy, intermediate and difficult levels. Mobilisation videos (safety with walking frame, mobilising with two elbow crutches and mobilising with one elbow crutch) will also be included. Material on health education and various aspects of their condition and any co-morbidities that they have will also be compiled for dissemination at the appropriate time as determined by the therapist’s interaction with the participants.

At the initial session, a thorough assessment will be carried out by asking the sequence of questions shown in Table 1.

**TABLE 1 T0001:** Assessment questions.

Number	Question
1	How are you doing at home?
2	What is your pain now?
3	How are you mobilising at home?
4	What distance are you managing to mobilise at home?
5	How are your exercises going on at home?
6	What exercises are you doing at home?
7	How are you managing activities of daily living (ADL) such as eating, dressing and personal hygiene activities?
8	What are you struggling with at the moment?

*Source:* [name], [name] & [name], 2020, *Standard operating procedure for the use of telehealth in COVID-19 scenario by physiotherapists at Chris Hani Baragwanath Academic Hospital*, Chris Hani Baragwanath Academic Hospital, Johannesburg.

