At subsequent telerehabilitation sessions (scheduled approximately 3–4 weeks apart), the therapist will obtain feedback on the patient’s functional status at home by using the subjective assessment framework. Follow-up sessions will consist of a re-assessment, patient education including pain management principles, medication adherence, importance of rehabilitation, ensuring that contraindications and precautions are understood and adhered to and scar management. Patient safety will also be addressed by giving suitable advice. Exercises will be prescribed, revised and progressed as required, and patients’ concerns will be addressed. Participant compliance will be monitored by encouraging the patient to keep a rehabilitation diary in which they record their exercises and progress as well as by corroborating the information with the family member. Weekly reminders will be sent, encouraging the patient to continue with their exercise programmes. Once patients have reached their functional goal, they can be discharged.

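### The arthroplasty plan tests compliance against outcome without starting status, so it cannot tell an effect of the exercises from confounding

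*Protocol article*

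**What the plan says.** The Statistical analysis section sets out an analysis for each objective. The first is "To determine the effects of telerehabilitation services for patients who have orthopaedics conditions (arthroplasty"). Under it the plan gives frequencies of the outcome domains, a comparison of hip with knee replacements, and tests of "bivariate associations between gender, age and compliance with the outcomes", which "will be assessed by using Chi squared test or Fisher’s exact test". It states no covariate, no stratification by starting status and no change from baseline.

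Other sections bear on this:

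- **Outcome measures (arthroplasty):** "The HOOS JR and KOOS JR will be used as an objective outcome measure for participants with arthroplasty". No time points are given.
- **Procedures (arthroplasty), initial session:** "At the initial session, a thorough assessment will be carried out by asking the sequence of questions shown in Table 1". Those questions cover pain, mobility, walking distance and daily activities.
- **Procedures (arthroplasty), follow-up:** "Participant compliance will be monitored by encouraging the patient to keep a rehabilitation diary in which they record their exercises and progress", with corroboration from a family member.
- **Methods and design:** "Exercise prescription will commence from the patients’ current level of function". The sample is purposive, no control group is described, and the sample size is left to a pilot.

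**The concern.** Compliance is something patients do after the programme starts, and it may depend on how they were at the start. Starting pain and mobility are also likely to predict later pain and mobility. When one factor drives both, a two-way table shows a relation between compliance and outcome that owes nothing to the exercises. Measuring compliance better would not cure this.

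The stake is interpretation. Hip versus knee, gender and age are patient characteristics. Of the arthroplasty tests stated, only the one on compliance involves exposure to the intervention. There is no control group and no stated before-after comparison. A small p-value here could therefore easily be taken as evidence that telerehabilitation works. A confounded null or reversed result could equally be taken as evidence that it does not.

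**Working it through.** The plan states no sample size, power or effect size for this analysis, so there is no figure of its own to reproduce. The check asks how often the planned test rejects when compliance has no effect at all.

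**Assumptions (none from the documents).** Starting status B is standard normal. Compliance and good outcome are each a median split of a normal variable. Their correlations with B, before the split, are r1 (compliance) and r2 (outcome). There is no direct link between compliance and outcome. The test is two-sided at 5%, and n is 60 to 150.

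**Size of the spurious difference.** The correlation between compliance and outcome induced through B is r1 × r2. The bivariate-normal formula then gives

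P(good | compliant) = 0.5 + arcsin(r1 × r2)/π, and P(good | not compliant) = 0.5 − arcsin(r1 × r2)/π.

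| r1, r2 | r1 × r2 | Compliant | Not compliant |
|---|---|---|---|
| 0, 0.5 | 0 | 50.0% | 50.0% |
| 0.1, 0.5 | 0.05 | 51.6% | 48.4% |
| 0.3, 0.5 | 0.15 | 54.8% | 45.2% |
| 0.4, 0.6 | 0.24 | 57.7% | 42.3% |
| 0.5, 0.7 | 0.35 | 61.4% | 38.6% |
| −0.3, 0.5 | −0.15 | 45.2% | 54.8% |

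The last row shows that if patients who start worse comply more, the spurious difference has the same size and the opposite sign.

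**Rejection rate of the unadjusted chi-squared test (simulation).**

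| r1, r2 | n = 60 | n = 100 | n = 150 |
|---|---|---|---|
| 0.3, 0.5 | 12.5% | 16.5% | 22.3% |
| 0.4, 0.6 | 22.2% | 36.1% | 47.4% |
| 0.5, 0.7 | 43.1% | 63.2% | 79.9% |

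With r1 = 0 the rate is about 5%. With r1 = 0.1 and r2 = 0.5 it is 6-7%.

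*Hand check at n = 100 with r1 = 0.4, r2 = 0.6.* The difference is 0.577 − 0.423 = 0.154. Its standard error is about √(0.25/50 + 0.25/50) = 0.10, so z is about 1.54. The chance of exceeding 1.96 is Φ(1.54 − 1.96) = Φ(−0.42), about 34%, close to the simulated 36.1%.

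A separate simulation at n = 50, 100 and 200 gave 12%, 16% and 28% for (0.3, 0.5), and 38%, 64% and 90% for (0.5, 0.7).

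**After adjustment for starting status.**

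- *B measured without error:* rejection returns to 4.6-5.8% with a linear model, and to 4-7% with a probit model in the separate simulation.
- *B measured with reliability 0.5 (assumed), score as outcome:* adjusted rejection is still about 8% to 54% over the grid in the second table.
- *Same reliability, outcome split at the median:* 14% at n = 100 with (0.4, 0.6), against 36.1% unadjusted, and 37% at n = 150 with (0.5, 0.7), against 79.9%. This is the like-for-like comparison with the planned test, because a model for the whole score detects any remaining bias more readily than a two-way table does.

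**The case against.** The plan calls these results associations, lists compliance beside gender and age, and describes its analysis as descriptive. It nowhere says that the compliance result will be read as a dose-response or as proof of effect. This stands as far as the wording goes. It does not dispose of the point, because the objective is worded in terms of effects, and the Discussion says the results will inform understanding of efficacy and will be used to advise policymakers on it.

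A reader might infer that a spurious association is bound to appear, and that it will favour compliance. The documents do not support this. They give neither correlation. Starting the prescription from the patient's current function, with exercises graded by difficulty, matches the task to the patient and could weaken any link between starting status and compliance. With no such link the test is nominal, and with a negative one the bias reverses.

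A reader might also infer that adjustment settles the matter. It does so only if starting status is measured without error. The Table 1 questions are open and would measure it imperfectly.

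Finally, the article does not say whether compliance is recorded before the outcome. That timing may be fixed in a fuller document and is not counted against the plan here. The choice of an unadjusted two-way test is different, because the article states it.

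**Conclusion.** The point holds in a conditional form. The stated test cannot distinguish an effect of the exercises from confounding by starting status, although the study already asks about that status at the first session. How much this matters is unknown. Under no true effect and n of 60 to 150, false rejection runs from about 5% (compliance unrelated to starting status) to about 80% (correlations 0.5 and 0.7, n = 150). The sample size, the correlations and the median splits are all assumptions. The defect is worth correcting because a bias in either direction makes the result uninterpretable under an objective about effects. It does not show that the study will report a false association.

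**What to change.** Replace the compliance cross-tabulation with a regression of the later score on compliance, fitted separately by joint (HOOS JR for hips, KOOS JR for knees), with starting status as a covariate. Define that covariate in one way for all patients. Use either the first-session pain and mobility answers from Table 1, or the first-session HOOS JR or KOOS JR score if it is taken for everyone. Do not mix the two. Report the compliance coefficient with its 95% CI, and state that it is an association and not evidence of effect.

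**Cost.** The Table 1 option needs no new question to patients, only a simple coding rule for the pain and mobility answers, fixed before analysis. Its downside is that these answers measure starting status imperfectly, so adjustment reduces the confounding without removing it. The score option would probably measure status better. Because the article states no time points for the score, it may require adding a first-session administration, which is a change to data collection and not only to the analysis wording.
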